**Summary of design of the proposed research project.**

#### Study participants

The Integrated University Health Network, known as the RUIS (*Réseaux universitaires intégrés de santé*), of *Université de Sherbrooke* caters to a population of over 1 million people, encompassing a vast territory including Sherbrooke and Montérégie areas. A pool of at least 35 FMGs in this coverage area did not participate in our Phase-1 project. We will enroll a total of 10 of these FMGs in Phase-2, from which 4-10 members (including at least 2 PCPs and 1 nurse) will participate in our study. When we will initially contact FMGs, we will propose to them a study assessing lifestyle management in primary care and its evolution over time. When we will be in contact with 2 interested FMGs, we will randomize them to the intervention or control groups. The first FMG will then be offered to participate in our obesity management system with preceptorships and virtual learning community. The control FMG will be offered practice monitoring without being aware of the intervention. Participants of each group will sign different consent forms.

As much as possible, we plan to evaluate participants from FMGs pairs of intervention and control groups concomitantly in order to avoid bias related to time of evaluation (due to seasonal effects on weight, campaigns of health promotion, high-impact scientific publications, etc.). Within each FMG, adult patients who present for follow-up will be offered by FMG clerical personnel to have their chart accessed by our team and to be contacted if eligible for the project. If they consent, their chart will be screened to verify if they had, during the past 2 years, at least 4 documented visits for the targeted disease group and at least 2 visits for the regular follow-up group, and if continued follow-up is planned or highly probable in the next 18 months. We aim to include in our study 22 patients per FMG in the targeted disease group, and 24 patients per FMG in the regular follow-up group (total of 460 patients). Patient numbers will be prospectively accrued within each patient category during the recruitment period and before preceptorship delivery for the intervention group, until targeted numbers are achieved. In order to minimize important potential biases, patients will be kept blinded regarding their FMG group and the study objectives related to the evaluation of this intervention.

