The impact of our program on patient’s care will be assessed by the comparison of patients’ outcome variables between those recruited from FMGs allocated to intervention and those recruited from FMGs allocated to no intervention. Similarly, the impact of our program on PCPs will be determined by the comparison of variables related to PCPs between those who received the intervention and those who did not. Univariate analyses will use two-tailed unpaired *t* tests to compare continuous variables and chi-square or Fisher’s-exact tests to compare categorical variables. Continuous variables that are not normally distributed will be log-transformed in order to ascertain normal distribution, whenever possible, or will be compared using two-tailed Wilcoxon tests. Multivariate analyses will also be used in order to adjust for baseline differences between groups, potential confounders and cluster effects of individual FMGs. Should differences between patients’ or PCPs’ groups be evidenced, Pearson correlation analyses will be performed to determine if such differences are related to a potentially mechanistic variable. For example, benefits in patients’ outcome variables will be correlated with changes in variables assessing attitude, perceptions, knowledge and/or better clinical practice for their primary care providers. An α level of 5% will be used for all analyses.

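### Patient-level tests and cluster-adjusted analyses stand at the same 5% level, and nothing makes the cluster-adjusted one decisive although FMGs are randomised

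*Protocol article*

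**What the plan says.** **Unit of randomisation (Study participants).** "We will enroll a total of 10 of these FMGs in Phase-2", and allocation is by pair: "When we will be in contact with 2 interested FMGs, we will randomize them to the intervention or control groups". Each FMG contributes 22 patients to the targeted disease group and 24 to the regular follow-up group, plus 4 to 10 health professionals.

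**Sample size (Sample size, data analysis and interpretation).** The Aim 1 primary variable, loss of at least 5% of initial weight, is sized on chi-square: 21% against 42%, 80% power, 30% loss, 220 patients. The Aim 2 primary variable, a recorded BMI, is sized on Fisher's exact test: 80% against 95%, 80% power, 240 patients.

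**Analysis (same section).** "Univariate analyses will use two-tailed unpaired" t "tests to compare continuous variables and chi-square or" Fisher's exact tests for categorical ones. Non-normal continuous variables are log-transformed or compared by Wilcoxon tests. Then: "Multivariate analyses will also be used in order to adjust for baseline differences between groups, potential confounders and cluster effects of individual FMGs". The paragraph closes: "An α level of 5% will be used for all analyses".

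The section does not say which of the two kinds of analysis decides the primary variables.

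**The concern.** Patients of one FMG share physicians, nurses and habits of practice, and the intervention is delivered to the FMG team. Their outcomes are therefore likely to be positively correlated. A test that counts patients as independent understates the variance of the arm difference whenever that correlation is positive.

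The plan holds one analysis that ignores the randomised unit and one that accounts for it, both at 5%. The only tests attached by name to the primary variables are of the first kind. If the two disagree, the text gives no basis for choosing, and the less demanding result could be reported as the finding. The article expects a beneficial result to speed adoption of the program as a practice model, so a false positive would have consequences.

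**Working it through.** **Inputs from the article.** 10 FMGs, taken as 5 per arm because allocation is by pairs; 22 and 24 patients per FMG; 30% loss; control proportions 21% (Aim 1) and 80% (Aim 2); level 5%, two-sided (stated for the t and Wilcoxon tests, taken as such for the others). **Assumed:** ICC of 0.01, 0.02, 0.05 and 0.10, since none is given.

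**Step 1. Reproduce the plan's figures.**
- Aim 1: two proportions, 0.21 against 0.42, pooled variance, no continuity correction, gives 76 per arm. 2 × 76 / (1 − 0.30) = 217.1, so 218, against 220 stated.
- Aim 2: 240 less 30% is 168, or 84 per arm. Exact Fisher power for 0.80 against 0.95 is 81.7%, against 80% stated. Without loss (120 per arm) it is 93.5%. That the 30% also applies to Aim 2 is an inference from this match.

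Both figures are those of an individually randomised trial, with no design effect.

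**Step 2. Aim 1, approximate type I error of the unadjusted chi-square.** Evaluable patients per FMG: 22 × 0.70 = 15.4, taken as m = 15.

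Design effect: DEFF = 1 + (m − 1) × ICC. True level ≈ 2 × [1 − Φ(1.96 / √DEFF)].

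| ICC | DEFF | Formula | Simulation |
|---|---|---|---|
| 0.01 | 1.14 | 6.6% | 6.8% |
| 0.02 | 1.28 | 8.3% | 8.4% |
| 0.05 | 1.70 | 13.3% | 13.4% |
| 0.10 | 2.40 | 20.6% | 20.8% |

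The simulation is beta-binomial with equal true proportions in both arms, 5 FMGs per arm and 100,000 replicates. A second run with 77 per arm (FMGs of 15 or 16) gave 6.9%, 8.4%, 13.9% and 21.4%.

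**Step 3. Aim 2, type I error of the unadjusted Fisher test** (same simulation, proportion 0.80). Evaluable patients per FMG: 24 × 0.70 = 16.8, taken as 17; or 24 with no loss.

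| ICC | 17 per FMG | 24 per FMG |
|---|---|---|
| 0 | 3.1% | 3.3% |
| 0.01 | 4.6% | 5.6% |
| 0.02 | 6.2% | 7.9% |
| 0.05 | 11.2% | 14.7% |
| 0.10 | 18.6% | 24.9% |

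Fisher is conservative without clustering, which absorbs the inflation at the smallest ICC.

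**Step 4. Tests that respect the FMG.** In the same simulations, a t test on the 10 FMG proportions (8 df) ran at 4.8% to 5.1%. A paired t test on 5 pairs (4 df) ran at 4.6% to 4.9%; the simulation put no correlation within pairs.

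**Step 5. Professionals.** With 4 to 10 per FMG, the Step 2 formula gives about 5% to 6% at ICC 0.01 and 6.8% to 10.4% at ICC 0.05. The inflation is smaller than for patients.

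**The case against.** The strongest reply is that the plan does deal with clustering. The t, chi-square and Fisher tests are labelled univariate, and the same paragraph commits to multivariate analyses that cover "potential confounders and cluster effects of individual FMGs". That stands. A reader might infer that the plan ignores the randomised unit altogether, or that its true error rate is simply well above 5%. The article supports neither. The first overlooks the multivariate sentence. The second needs the unadjusted tests to be decisive and the ICC to be about 0.02 or more. At ICC 0.01 the excess is small for chi-square and absent or slight for Fisher.

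Sizing a trial on a simple test does not prove that this test will decide it. That also stands: the sample-size paragraph shows which tests are named for the primary variables, not which one governs. The missing design effect there is a separate matter of power.

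A reader might go further and fault the multivariate route, on the ground that FMG as a fixed factor would leave the arm effect inestimable, or that uncorrected robust errors are too small with 10 clusters. The article proposes neither model, so these are not criticisms of it. The exact cluster model is the kind of detail that an article may leave to the full plan.

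What the reply does not remove is the lack of any order of precedence. The article fixes tests and a level, and one of the two kinds of analysis that it fixes has the wrong error rate for this design.

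**Conclusion.** The point holds in conditional form. The section sets unadjusted patient-level tests beside cluster-adjusted analyses at one 5% level and does not say which decides. If the unadjusted tests decide, then over an assumed ICC of 0.01 to 0.10 the Aim 1 chi-square test has a true type I error of about 7% to 21%. The Aim 2 Fisher test has about 5% to 19% with 17 evaluable patients per FMG, or 6% to 25% with 24. If the cluster-adjusted analysis decides, and its method suits 10 clusters, the level stays near 5% and the concern falls away.

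The figures rest on the assumed ICCs, equal FMG sizes, 5 FMGs per arm and a beta-binomial model. This goes beyond missing detail, because a test named in the plan would carry the wrong level for a cluster-randomised comparison.

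**What to change.** State in the data-analysis section that the primary test for each arm comparison is made at FMG level, or accounts for FMG, with a small-sample correction suited to 10 clusters. Any one of these would serve, chosen before outcome data by arm are seen:
- a t test on the 10 FMG proportions or means (8 df);
- its paired version on the 5 randomised pairs (4 df);
- a mixed model with FMG as a random effect and small-sample degrees of freedom.

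Report the cluster-adjusted difference with its 95% confidence interval and the ICC. Keep the patient-level univariate tests as descriptive only. Apply the same rule to the health-professional outcomes.

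**Cost.** Only wording changes, but intervals widen and nominal power falls. With 77 evaluable patients per arm in Aim 1, simulated power of the 8-df t test for 21% against 42% is about 71% at ICC 0, 65% at 0.01, 60% at 0.02, 49% at 0.05 and 38% at 0.10, against the planned 80%.

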### Sample size, data analysis and interpretation

According to AIM 1, our primary variable of interest is the proportion of obese or overweight subjects with HTN, DM2 or IGT who will lose least 5% of their initial weight after eighteen months. Assuming that 30% drop-out or provide incomplete data, our study needs to recruit 220 obese or overweight subjects with HTN, DM2 or IGT in order to achieve 80% power (using chi-square) to detect a doubling in the proportion of those who will lose at least 5% of their initial weight, based on a proportion of 21% in the control group (which is the average proportion observed in the control groups of two of our previous studies) [32,33,67] and 42% in the intervention group (which represent half of the average benefits found in these two studies compared to control groups) (***AIM 1***). Similarly, 240 unselected patients provided 80% power (using Fisher’s-exact test because of small minimum expected cell size) to detect an improvement of the proportion of these patients who have a reported measure of BMI from 80% in the control group (based on reported practice in our previous participants) to 95% in the intervention group (which is close to the 100% recommended by the CCPGO) (***AIM 2***). For AIM 2, our primary variable of interest is the proportion of unselected patients who have a reported measure of BMI, which defines obesity according to WHO and is therefore essential for the screening of obesity.

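### The planned Pearson correlations between patient benefit and provider change carry no arm term, so on the natural reading the programme's effect on both can pass for a mechanism

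*Protocol article*

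**What the plan says.** The section on sample size, data analysis and interpretation sets a sequence. Patients, and separately providers, are first compared between arms. If a difference is found in either, "Pearson correlation analyses will be performed to determine if such differences are related to a potentially mechanistic variable". The example given is that patient benefits "will be correlated with changes in variables assessing attitude, perceptions, knowledge and/or better clinical practice for their primary care providers". The section closes with "An α level of 5% will be used for all analyses".

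The sentence before this step says that multivariate analyses will adjust for baseline imbalance, confounders and FMG cluster effects. It does not extend that adjustment to the correlations.

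Three other places bear on the step:

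- The Hypothesis section makes mechanism a formal hypothesis (number 3): the benefits are to come about through providers' confidence, competence and clinical practice.
- The section on evaluation of health professionals schedules the provider questionnaires in both arms and adds that the results will be correlated with patient outcome.
- The preliminary-data section reports that provider confidence, attitude and self-efficacy rose after the preceptorship in Phase 1, so the investigators expect a positive shift in provider scores.

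Nowhere does the article say whether the correlation is computed across arms or within them, or whether the unit is the patient, the provider or the FMG.

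**The concern.** The step is run when the arms differ. If the programme raises provider scores and also improves patient outcomes, arm is a common cause of both. Intervention patients then sit high on both variables and control patients low on both, and a correlation across the two arms is positive even if a provider's change has no bearing on that provider's patients. The correlation largely restates that the programme moved two things.

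At stake is the reading of hypothesis 3. Attitude, perceived self-efficacy, knowledge and practice are all targets of the programme. Any of them that the programme shifts would tend to correlate with patient benefit, whether or not it matters to patients, so the analysis cannot tell them apart. The article expects decision-makers to use the results, and a supposed mechanism could steer which component of the programme is kept.

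**Working it through.** **Inputs from the protocol article.** Control response "based on a proportion of 21% in the control group"; "42% in the intervention group"; "Assuming that 30% drop-out or provide incomplete data"; 220 targeted-disease patients recruited; 10 FMGs randomised in pairs, so 5 per arm; 4–10 professionals per FMG; α 5%. The article specifies two-tailed t and Wilcoxon tests; two-sided testing is taken for the correlation as well.

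**Assumptions, not in the article.** A between-arm shift in provider score of d = 0 to 1.5 SD; 4 providers per FMG; intraclass correlations (ICCs) where stated; both arms analysed together.

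**Step 1: the plan's own figure.** n per arm = [1.96·√(2·0.315·0.685) + 0.8416·√(0.21·0.79 + 0.42·0.58)]² / 0.21² = (1.288 + 0.539)² / 0.0441 ≈ 76. Then 2 × 76 = 152 and 152 / 0.70 ≈ 218, against 220 stated. The sample size reproduces. Evaluable patients: 220 × 0.70 = 154.

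**Step 2: the correlation produced by arm alone.** With equal arms and no link within arm, the covariance of score and response is 0.25 × d × 0.21. The score variance is 1 + 0.25d² and the response variance is 0.315 × 0.685 = 0.2158 (SD 0.4645).

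- d = 0.5: r = 0.02625 / (1.031 × 0.4645) = 0.055
- d = 1.0: r = 0.0525 / (1.118 × 0.4645) = 0.101
- d = 1.5: r = 0.07875 / (1.25 × 0.4645) = 0.136

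By Fisher's z with √(154 − 3) = 12.29, the expected test statistics are 0.67, 1.25 and 1.68. The chance of exceeding ±1.96 is about 10%, 24% and 39%.

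**Step 3: simulation of the same set-up.** Patients share provider values, and response is independent of provider score within arm. There were 2,000 trials per row, with a Monte Carlo error of about 1 percentage point. The entries are false-positive rates for one correlation.

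| Provider shift (SD) | Both arms together | Same, only after a significant arm difference in response | Arm means removed |
|---|---|---|---|
| 0 | 7% | 8% | 5% |
| 0.5 | 12% | 13% | 5% |
| 0.8 | 20% | 23% | 5% |
| 1.0 | 25% | 30% | 5% |
| 1.5 | 40% | 47% | 6% |

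Repeat simulations gave 13–14%, 30–31% and 47–49% in the third column for shifts of 0.5, 1.0 and 1.5 SD. The simulated mean correlations (0.055, 0.102, 0.137) agree with step 2.

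**Step 4: does the unit matter?** Rates after the trigger, at 0.5 / 1.0 / 1.5 SD:

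- provider averages: 9% / 23% / 37%
- FMG averages (10 points): 14–17% / 35–40% / 52–57% across simulations

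Averaging takes away the repeated values and leaves the arm effect.

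**Step 5: clustering.** With no arm effect on either variable, FMG and provider ICCs of 0.02–0.05 each give 5–8%, and 0.10 each gives 12%. With a 1.0 SD shift and ICCs of 0.02–0.05 each, the rates are 26–30% with arms together, 31–36% after the trigger and 6–10% with arm means removed. Arm is the larger source of error; clustering adds to it and is not cured by the arm term.

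**The case against.** The strongest reply is that the article never says the arms are pooled or that one provider's value is repeated over many patients. A within-arm correlation would fit the wording, and an article may leave such detail to the full protocol. The neighbouring sentence on multivariate analysis shows that confounding and clustering were recognised. This stands in part: pooling and the patient-level unit are inferences. But the article does fix the method, the trigger and the conclusion to be drawn. The differences it wants explained are between arms, and provider scores are collected in both. Only a within-arm or arm-adjusted analysis escapes the problem, and neither is stated.

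A second reply is that the programme is delivered to professionals and patients are blinded to it, so benefit must run mainly through providers. That narrows the question to which provider variable matters. The unadjusted correlation is ill suited to that question, because every variable the programme shifts will tend to correlate with benefit.

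Third, the step is secondary and partly hedged in wording, and qualitative interviews also examine the change process. This stands, and it limits the weight of the point.

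A reader might also infer more than the documents support:

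- *That the analysis is bound to find a false mechanism whenever the programme works.* At patient level the rate stays below half in every case examined. It passes half only for FMG averages at a 1.5 SD shift.
- *That repeated provider values are the main fault.* They are the smaller part, and their effect depends on assumed ICCs.
- *That Pearson correlation is invalid because 5% weight loss is binary.* With a binary variable it is the point-biserial correlation, and with arm means removed it held 5–6% here. Many of the listed outcomes are continuous in any case.

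**Conclusion.** The concern holds in limited form. As written, the step is an unadjusted correlation, run because the arms differ, and used to decide mechanism. Read across both arms, it has a false-positive rate of about 14–47% per correlation after the trigger, for assumed provider shifts of 0.5–1.5 SD, against a nominal 5%. Averaging to FMG level does not remove the inflation. Shared provider values and FMG clustering add a smaller amount.

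These sizes rest on the assumed shifts, 4 providers per FMG, pooled arms, and a trigger based on the patient outcome; the article also allows a trigger based on provider differences. The direction does not depend on the exact shift, since any programme effect on both variables induces the correlation. The primary comparisons for Aims 1 and 2 are not touched. The change should be made, but the trial's main result does not depend on it.

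**What to change.** Replace the unadjusted Pearson step with a regression of patient outcome on provider change that includes arm as a covariate. State the unit, and how each patient is linked to one or more professionals, since physicians and nurses share care. Account for FMG clustering by a method suited to 10 clusters, for example a mixed model or estimating equations with a small-sample correction. A model with separate random effects for FMG and provider may be more than about 15 evaluable patients per FMG (154 / 10) can support. Report the arm-adjusted association with its confidence interval and label it exploratory. Drop the claim that the step determines mechanism.

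The cost is analysis wording and a little programming; no new data are needed. Intervals will be wider and fewer mechanism results will be significant. If the programme shifts all providers alike, little provider variation is left within arm and the adjusted association has little power. It therefore neither proves nor excludes mediation, and the report should say so.

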### Knowledge translation plan *(Aim 5)*

It is worth mentioning that our research program is optimal to allow knowledge translation (KT) and application throughout the entire research process. The preceptorship experience in itself is a knowledge translation activity for health professionals. Our group is also actively involved in developing a National Preceptorship program with the Canadian Obesity Network (CON) and this could evolve in the development of a national virtual community and improvements in CON CME activities. Evidence-based information on patient outcomes generated by our study will have a great impact on knowledge transfer: if beneficial, it would accelerate the implementation of such programs as practice models; and if benefits are less than expected, it will orientate to program modification.

However, research by itself does little to induce change (except for participants) and thus, results have to be diffused to interested audiences. We have access to specialized communication resources from the CHUS Research Center and CON to develop an optimal strategy for dissemination of results and potential applications.

Our research is relevant to PCPs, nurse coordinators, specialists in various disciplines and associated health professionals, CME departments, public health directorates, health-system decision-makers. We will reach out to these parties through linkage and exchange activities, including presentation of study results at scientific meetings and publication in scientific journals, but also by direct reports to decision-makers and health policy stakeholders. A clear summary of research results, including key messages targeted for each selected audience and synthesized results (divided by themes) will be available (printed and on our web site). Local and national media will be invited to press conferences and we will schedule private meetings with important decision-makers to whom our findings are relevant.

